## Abstract

**Background:**

Polycystic Ovary Syndrome (PCOS) is an endocrine disorder in women of reproductive age with an estimated prevalence of 5–20% of premenopausal women. The clinical symptoms common to PCOS include menstrual dysfunction, hyperandrogenemia, hirsutism, polycystic ovaries, insulin resistance, and hyperinsulinemia. Women with PCOS are at an increased risk of infertility, obesity and type 2 diabetes mellitus. Insulin resistance and hyperinsulinemia are believed to be key contributing factors to the pathogenesis of PCOS; excessive amounts of insulin are directly associated with the increased ovarian production of androgens and metabolic features of PCOS. Pulse-based diets (e.g., beans, chickpeas) are associated with improved glycemic control and have insulin lowering effects. The purpose of this study is to determine whether a pulse-based diet is more effective than the diet recommended by the National Cholesterol Education Program. The primary outcomes of this study are disease measures related to PCOS, with secondary outcomes including measures related to metabolic syndrome.

**Methods:**

Women with symptoms of PCOS will be recruited for the study and a diagnosis of PCOS will be determined by an obstetrician-gynecologist. Women with PCOS will be randomly assigned to receive either a pulse-based diet or the National Cholesterol Education Program therapeutic lifestyle changes (TLC) diet for 16 weeks while participating in an aerobic exercise program. One hundred participants will be required (drop-out rate of 32%) for recruitment to provide 80% power for detecting a significant difference in fasting glucose (*p* < 0.05). Measures related to infertility, metabolic syndrome, quality of life, dietary intake and physical activity will be assessed pre- and post-intervention with follow up assessment at 6- and 12-months post-intervention.

**Discussion:**

Polycystic ovary syndrome is the most common endocrine disorder in women of reproductive age and there is currently no recommended diet for this population of women. The multidisciplinary nature of this study, including determination of measures related to metabolic syndrome, infertility and physical activity provide a comprehensive assessment of any benefits associated with a pulse-based diet in women with PCOS. The results of this study will help in providing evidence-based recommendations for the optimum diet to reduce symptoms associated with PCOS.

**Trial registration:**

NCT01288638. Trial registered January 13, 2011.

## Background

Polycystic Ovary Syndrome (PCOS) is an endocrine disorder in women of reproductive age with an estimated prevalence of 5%–20% of premenopausal women [1, 2]. The clinical symptoms common to PCOS include menstrual and ovulatory dysfunction, hyperandrogenemia, hirsutism, polycystic ovaries, insulin resistance, and hyperinsulinemia [3]. A diagnosis of PCOS is associated with an increased risk of infertility, dysfunctional bleeding, endometrial carcinoma, obesity, type 2 diabetes mellitus, dyslipidemia, hypertension, and possibly cardiovascular disease [3–6]. The pathogenesis of PCOS is not fully understood; however, insulin resistance and associated hyperinsulinemia that affect 50–70% of women with PCOS are believed to be key contributing factors [7, 8]. Insulin resistance and the subsequent production of excessive amounts of insulin are directly associated with the increased ovarian production of androgens and the features of PCOS [9]. Lifestyle modifications, including diet and exercise, are currently the first-line treatment recommended for women with PCOS [10]; however, there are currently no specific diet recommendations for women with PCOS.

Pulses (e.g., lentils, chick peas, split peas, beans) are high in fiber, have a low-glycemic index, are low in fat, and contain high quality protein. Pulse-based diets are also effective for lowering fasting blood glucose, insulin and blood pressure [11, 12]. These nutritional qualities are important for reducing the risk of metabolic-related and cardiovascular diseases such as diabetes. Pulse consumption has been shown to result in positive effects in individuals at risk for metabolic syndrome [13]. Although clinical trials have demonstrated positive health effects of dietary pulse consumption, some studies have limitations such as insufficient follow up time [11] as well as lack of consistency in dose and disease phenotype [12]. Furthermore, the need for more ‘real world’ trials measuring compliance has been highlighted [11].

In women with PCOS, insulin resistance has been shown to be independent of obesity [14]. Hyperinsulinemia and adiposity exacerbate metabolic and reproductive abnormalities in women with PCOS [15–19]; therefore, our objective is to test the hypothesis that a pulse-based diet can improve symptoms related to metabolic syndrome, infertility and menstrual cycle regularity in women with PCOS. The purpose of this manuscript is to detail the study design and methodology used in a randomized clinical trial involving a diet and exercise intervention in women with PCOS.

The primary outcome measures of this study are disease measures related to PCOS including sex hormones and numbers of ovarian follicles. Secondary outcomes of this study include measures related to metabolic syndrome, quality of life, physical activity and diet.

## Methods

### Design overview

The present study is a single-blind, parallel, stratified-randomized clinical trial. The work is funded by Saskatchewan Pulse Growers and Agriculture Agri-Food Canada. The study design is detailed in Fig. 1. The aim of the study is to determine the effect of a pulse-based diet compared to a healthy control diet on disease measures related to PCOS as well as metabolic syndrome risk factors in women with PCOS while they are enrolled in an exercise program. After the study coordinator obtains informed signed consent, study participants will be assessed to determine whether they have PCOS. Women diagnosed with PCOS will undergo baseline testing followed by a 2-week lead-in period on the healthy control diet (therapeutic lifestyle changes (TLC) recommended by the National Cholesterol Education Program). Following the lead-in, participants will repeat baseline blood measures followed by randomization to either the pulse-based diet or the TLC diet for 16-weeks while participating in an aerobic exercise program. Blood measures will be assessed after 9-weeks and at the end of the 16-week intervention, participants will undergo end of intervention testing; follow-up measures will also be assessed at 6-months and 12-months.

**Fig. 1 Fig1:**
[figure not shown]
CONSORT flow diagram of study timeline for pulse-based diet intervention in women with polycystic ovary syndrome

The primary outcome of this study is to determine the effectiveness of a pulse-based diet compared to a healthy control diet (TLC diet) for improving PCOS disease measures including sex hormones, menstrual cycle length and, numbers of ovarian follicles. Secondary outcomes include 1) Measures of metabolic syndrome including liver adiposity; 2) Body composition; 3) Quality of life; 4) Physical Activity; and, 5) Diet.

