### Sample size

A pilot study (unpublished) was carried out on preliminary data from 41 women with PCOS randomized to the pulse-based or TLC diet. Thirteen of the 41 women dropped out of the study giving a dropout rate of 32%. Changes in fasting glucose following the intervention (*n* = 28) was used to determine the required sample size for recruitment into the study. Changes in the mean fasting glucose were -0.18 and 0.14 mmol/L for the pulse-diet group and TLC group, respectively, with a population standard deviation of 0.46 and an effect size of -0.70. The pilot data provided 80% power for detecting a significant difference in fasting glucose concentration between groups (*p* < 0.05) following the intervention. It was determined 34 participants per group would be required for the study. Due to the dropout rate of 32%, the recruitment of 100 participants (i.e. 50 per group) was determined necessary.

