### Reproductive measures

Ovarian and uterine morphology, including the ovarian volume and the number of ovarian follicles, endometrial thickness and endometrial pattern will be assessed at the Royal University Hospital via transvaginal ultrasound using a GE Voluson® 730 Pro (Zipf, Austria). The ultrasound examination will be timed to occur during days 1-5 of participants’ menstrual cycle, with the first day of menstrual bleeding defined as day 1. Women who do not have cyclical menstrual bleeding will be seen at random times. Levels of estradiol, progesterone and an androgen index (ratio of testosterone to sex hormone binding globulin) will be assessed clinically at the Royal University Hospital and the Saskatchewan Provincial Laboratory.

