## Discussion

The present study is designed to determine whether a pulse-based diet is equally or more effective than a healthy control diet at reducing symptoms related to metabolic syndrome and reproductive dysfunction in women with PCOS. Although diet intervention studies in women with PCOS have been carried out, this is the first to determine the effects of a pulse-based diet in this population. The study design outlined has several features contributing to the novelty of this research. The diagnoses of PCOS used in dietary intervention studies have primarily used the Rotterdam criteria which defines polycystic ovaries as >12 follicles [42–44]. Recently, it has been suggested that the follicle count recommended by the Rotterdam criteria is too low due to improvements in resolving power of ultrasound images and an accurate diagnosis of PCOS requires a threshold of 26 follicles [21, 45]. The enhanced criterion used in the present study may allow for a more accurate representation of the PCOS population compared to similar intervention studies.

The present study takes a multi-disciplinary approach by incorporating measures from nutrition, physiology, kinesiology, psychology, and reproductive medicine. This approach allows for a comprehensive integration and association of the various components of PCOS which may lead to a better understanding of this multi-faceted syndrome. The inclusion of Kinesiology in the study produces unique data sets such as the use of accelerometers to quantify levels of activity which have been determined via self-reported questionnaires in previous reports [46, 47], 7-day activity records [48], physical activity recall [49] interviews [50], and Pedometer [51]. There is a paucity of physical activity data using accurate and objective measures in women with PCOS [52] and the present study utilizes information obtained using both physical activity questionnaires and accelerometers.

The baseline data collected as necessary for the analyses of the dietary intervention will also serve to characterize women with PCOS. The magnitude of our study with over 100 participants providing baseline measures, will result in an all-inclusive profile of women with PCOS which characterizes their lifestyle (i.e., diet including pulse consumption and exercise), quality of life, various health indicators for risk of disease (e.g., blood parameters, anthropometry, body composition) and infertility.

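### The primary outcome is an open list that differs between sections, has no named measure or time point, and is not what the trial was sized on; the Discussion also widens the aim to equal effectiveness without a margin

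*Protocol article*

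**What the plan says.** The primary outcome is described in three places in the Protocol article.

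- **Abstract, Background:** only a class, disease measures related to PCOS, with no variable named.
- **Background (closing paragraph):** disease measures "including sex hormones and numbers of ovarian follicles".
- **Methods, Design overview (text after Fig. 1):** "improving PCOS disease measures including sex hormones, menstrual cycle length and, numbers of ovarian follicles".

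Reproductive measures specifies the hormones: "Levels of estradiol, progesterone and an androgen index", the index being testosterone over sex hormone binding globulin. Data management and analysis applies a group-by-time ANOVA (baseline, 9 and 16 weeks) to the dependent variables and singles none out. Further measurements follow at 6 and 12 months.

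In Sample size, the pilot change in fasting glucose "was used to determine the required sample size for recruitment into the study". The stated power is for "detecting a significant difference in fasting glucose concentration between groups (*p* < 0.05) following the intervention". The Design overview puts measures of metabolic syndrome among the secondary outcomes, and fasting glucose is listed under Measures related to metabolic syndrome.

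On the aim, the Abstract sets out to "determine whether a pulse-based diet is more effective than the diet recommended" by the National Cholesterol Education Program. The Discussion says the study is designed to "determine whether a pulse-based diet is equally or more effective than a healthy control diet".

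**The concern.** A primary outcome is meant to settle, before the data are seen, which result decides the trial. Here a reader cannot tell whether menstrual cycle length is primary, which hormone counts, or which visit counts. Both lists are introduced by *including*, so neither is closed. Whichever reproductive measure turned out favourably could later be presented as the primary result without departing from the text.

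The stated power gives no anchor, because it belongs to a different and secondary measure.

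The Discussion wording adds a second route to a positive conclusion: a non-significant difference could be described as equal effectiveness, although the article gives no margin and sizes the trial to detect a difference.

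**Working it through.** **1. The plan's own figure.** From Sample size: mean changes −0.18 and 0.14 mmol/L (difference 0.32), SD 0.46, 80% power, p < 0.05 (taken as two-sided; the article does not say).

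- Standardised effect: 0.32 / 0.46 = 0.696, matching the stated 0.70 in size.
- A two-sample t-test needs 33.4, so 34 per group; power at 34 is 80.7%. A one-sided test would need 26 (normal approximation) and does not fit.
- Dropout: 34 / (1 − 0.32) = 50 per group, 100 in total.

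The stated size is reproduced, but for fasting glucose. No effect size, SD or power is given for any hormone, follicle number or cycle length.

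**2. Counting candidate primary variables.** Estradiol, progesterone and androgen index (3) + follicle number (1) + menstrual cycle length (1) = 5. Because the lists are open, this is a minimum.

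**3. Is cycle length measured as an outcome?** It is absent from Baseline measures, Intervention, Maintenance, Compliance (the daily log) and Reproductive measures. It appears only as a self-reported history used for diagnosis (Population). Reproductive measures expects some women without cyclical bleeding; for them a cycle length is undefined.

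**4. Chance of at least one false-positive primary result.** This assumes no true effect, five tests, each two-sided at 0.05, with no adjustment. If independent: 1 − 0.95^5 = 0.226. With equal pairwise correlation (an assumption, since the article gives none), by simulation of normal test statistics, 400,000 draws each:

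| Correlation | At least one of five |
|---|---|
| 0 | 22.6% |
| 0.3 | 20.8% |
| 0.5 | 18.3% |
| 0.7 | 14.8% |
| 0.9 | 10.1% |

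Counting only false positives in one pre-set direction per measure gives about 12% (independent) down to 5% (correlation 0.9).

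**5. What the design can say about equality.** With 34 per group, the 95% CI half-width for glucose is t(0.975, 66) × 0.46 × √(2/34) = 1.997 × 0.46 × 0.2425 = 0.22 mmol/L, or 0.48 SD for any outcome. Relative to the planned difference: 0.223 / 0.32 = 70%. So an observed difference of exactly zero would leave differences up to about 70% of the planned effect unexcluded in either direction.

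**6. Price of keeping five primaries.** At the strictest Holm step (0.05 / 5 = 0.01), 34 per group has 58.7% power for one measure at a standardised effect of 0.696. For 80% power, 50 evaluable per group are needed: 100 / 0.68 = 147.1, about 148 recruited. This borrows the glucose effect size purely as an illustration.

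**The case against.** The strongest reply is that this is a condensed article. A multiplicity rule, a hierarchy or the method of recording menstrual cycles may be in the full protocol or analysis plan. That stands: the article's silence on adjustment is not itself a fault, and the 23% is conditional on unadjusted testing. It does not cover the disagreement between the Background and Design overview lists, and no adjustment rule can be applied to a list that is not closed.

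It can also be said that *including* makes neither list exhaustive, and that the Background objective mentions menstrual cycle regularity. This softens the contradiction, but leaves the open-endedness in place.

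Three stronger readings are tempting and not supported:

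- **That a false primary claim is likely.** Roughly 10% to 23% is two to four and a half times nominal, but far from likely.
- **That cycle length would have no value for the women who matter most.** The problem is confined to women without cyclical bleeding, whose share is not given. Women with long cycles can complete two or three in 112 days (112 / 35 = 3.2). Because the ultrasound is timed to cycle days 1–5, bleed dates must be known for cycling women.
- **That the trial has been turned into an equivalence study.** The wording is one Discussion sentence. The Design overview is neutral, the sample size is for a difference, and the Discussion closes by asking whether the diet can better serve these women.

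On the interval, a CI centred on zero at 34 per group does exclude the full 0.32. If all 50 per group were analysed, the half-width would fall to 1.984 × 0.46 × √(2/50) = 0.18 mmol/L (0.40 SD), about 57% of 0.32. That is still too wide to support equality without a margin.

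**Conclusion.** The point holds, within limits. The primary outcome is open-ended, stated differently in three places and tied to no single measure or time point. One of its named components has no described outcome measurement. At least five variables qualify. If all were tested at 0.05 without adjustment, the chance of at least one false-positive primary result would be up to about 23% (18% at correlation 0.5, 10% at 0.9) against 5%; this rests on five tests and assumed correlations.

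The 80% power belongs to fasting glucose, so no listed primary measure has stated power.

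The equality wording in the Discussion is a smaller matter, but the design cannot support it: at 34 per group a zero difference leaves up to about 70% of the planned glucose effect unexcluded.

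**What to change.** 1. Use one closed primary list, worded identically in the Abstract, Background and Design overview.
2. Before unblinded data are seen, name one primary measure at week 16, tested two-sided at 0.05, with the other reproductive measures secondary. Alternatively, apply Holm across the closed list.
3. State in Sample size that the power figure applies to fasting glucose and not to the primary measure.
4. Keep menstrual cycle length as primary only if its recording and the handling of women without bleeding are defined; otherwise make it secondary.
5. In the Discussion, delete *equally or*, or state that a non-significant difference will not be read as equivalence.

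**Cost.** The changes are to wording, but the study is ongoing, so the choice should be dated and justified. Measures moved to secondary lose headline standing. Under Holm, power per measure falls, to 58.7% at the strictest step in the illustration above. Naming one primary keeps alpha at 0.05, but its power remains unstated until an effect size and SD for that measure are supplied.

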### Setting

The study will be conducted in Saskatoon, SK Canada and is a joint project between investigators in the Colleges of Pharmacy and Nutrition, Kinesiology, and Medicine at the University of Saskatchewan. All medical diagnostic appointments will take place at the Royal University Hospital in Saskatoon. Other assessments will take place at a College of Kinesiology research facility on the University of Saskatchewan campus. Ethics approval and approval for all protocol amendments will be obtained via the University of Saskatchewan Research Ethics Board. All study procedures will be conducted in full compliance with the Tri-Council Policy Statement on the Ethical Conduct for Research Involving Humans, the Declaration of Helsinki on ethical principles for medical research involving humans, and in compliance with the guidelines of the International Conference on Harmonization on Good Clinical Practice.

### Recruitment

Women will be recruited via regular posts on the University of Saskatchewan student and faculty online bulletin board. Women will also be recruited by posters located throughout the University of Saskatchewan, physician offices, health care establishments, and advertisements in local newspapers. The study coordinator will also meet with primary care physicians at clinics in Saskatoon to provide information about the study as well as to distribute consent forms to give to potential participants. Recruitment will also take place via the clinical practice of one of the researchers involved in the study ([name]).

### Population

Eligibility criteria require that volunteers be 18–35-year old females with symptoms of missed or irregular menstrual periods. Participation in the intervention is based on a clinical diagnosis of PCOS. Each participant will be assessed clinically to confirm the diagnosis of PCOS which will be made by an obstetrician-gynecologist specializing in PCOS using criteria specified in the PCOS report of the Androgen Excess-PCOS Society Task Force [3]. Diagnosis of PCOS requires presence of two of the three diagnostic criteria as defined by the Rotterdam consensus: A self-reported history of cycles >35 days in length, hyperandrogenism as defined by a Ferriman and Gallwey score of >6 or hyperandrogenemia [3], as well as polycystic ovaries (PCO), defined as >25 follicles visualized by transvaginal ultrasonography to reflect the newest guidelines for PCO recommended by the Androgen Excess and Polycystic Ovary Syndrome Society [20, 21]. Women with the following conditions will be excluded: Taking anti-seizure or anti-psychotic medications known to induce development of insulin resistance and polycystic ovaries; untreated hyperprolactinemia or thyroid disease; or, excessive adrenal androgen production confirmed by a diagnosis of congenital adrenal hyperplasia, Cushing’s syndrome, or an adrenal tumor. Women using hormonal birth control methods during the prior 3 months or who have a medical condition limiting exercise or consumption of a pulse-based diet (allergies or intolerances) will be excluded. Women will also be excluded from the study if they have an uncontrolled medical condition that interfered with ovarian or systemic hormone production, are pregnant or breastfeeding, or reside outside of the local geographic area.

### Sample size

A pilot study (unpublished) was carried out on preliminary data from 41 women with PCOS randomized to the pulse-based or TLC diet. Thirteen of the 41 women dropped out of the study giving a dropout rate of 32%. Changes in fasting glucose following the intervention (*n* = 28) was used to determine the required sample size for recruitment into the study. Changes in the mean fasting glucose were -0.18 and 0.14 mmol/L for the pulse-diet group and TLC group, respectively, with a population standard deviation of 0.46 and an effect size of -0.70. The pilot data provided 80% power for detecting a significant difference in fasting glucose concentration between groups (*p* < 0.05) following the intervention. It was determined 34 participants per group would be required for the study. Due to the dropout rate of 32%, the recruitment of 100 participants (i.e. 50 per group) was determined necessary.

